**PROTOCOL SYNOPSIS**

Title of Trial: Bright Light Therapy Efficacy for Depressive Symptoms Following Cardiac Surgery: Pilot Trial (BEAM-P)

Short Title of Trial: BEAM-P

Sponsor-Investigator: [name] MPH (Jewish General Hospital, Montreal, QC)

Trial Sites: Single centre

Trial Phase: IV

Primary Objective: (1) To assess the feasibility of conducting a full efficacy trial.

Methodology: Randomized (1:1), controlled trial

Sample Size: 38 participants

Study Population: Cardiac surgery patients experiencing moderately depressive symptoms.

Trial Arms: (1) Bright light therapy lamp (10,000 lux light intensity); (2) Modified dim lamp (500 lux)

Treatment Duration: 4 weeks

Follow-up Duration: 12 weeks (inclusive of the 4 week treatment period)

# 1. TRIAL OBJECTIVES AND PURPOSE

## 1.1 Overall Trial Objective

The Bright Light Therapy Efficacy for Depressive Symptoms Following Cardiac Surgery: Pilot Trial (BEAM-P) is a randomized controlled trial (RCT) that seeks to assess the feasibility of conducting a full trial which would assess the efficacy of Bright Light Therapy (BLT) for improving depressive symptoms post-cardiac surgery.

## 1.2 Primary Objective

To assess the feasibility of conducting a full trial, including assessment of recruitment rate, retention rate, adherence, process time, and potential additional data values that should be measured.

## 1.3 Rationale

More than 50,000 Canadians undergo cardiac surgery each year, and of these patients, at least 15-20% experience depression. The rate of depression in this population is almost three-fold greater than in the general population, and tends to be persistent. Unfortunately, depression remains under-recognized and undertreated. Depression has widespread health, economic, and social consequences. A study conducted in Quebec found that the costs of treating myocardial infarction (MI) patients who are depressed are 41% higher than for non-depressed patients. Treating depressive symptoms in cardiovascular patients can substantially contribute to reducing healthcare expenses. Cardiovascular patients with depression have also been found to be at greater risk of morbidity and mortality than non-depressed cardiovascular patients (hazard ratio 2.2). Risk of mortality in MI patients with depressive symptoms is significantly increased in the first 6 and 18 months post-MI. Even mild depressive symptoms (not considered clinically significant) have been shown to increase the risk of death after an acute MI. Depressive symptoms in cardiac patients have severe consequences and must be adequately treated in order to reduce the risk of morbidity and mortality. Novel efficacious treatments for depressive symptoms are urgently needed.

BLT may represent an innovative and effective method for reducing depressive symptoms in cardiac surgery patients. BLT has previously been shown to decrease depressive symptoms in individuals with seasonal and non-seasonal depression. A Cochrane review of BLT for non-seasonal depression concluded that BLT was significantly more effective at reducing depression than placebo and is a promising therapy for non-seasonal depression. BLT for non-seasonal depression has been shown to produce benefits in the range of 12-35% reduction in depressive symptoms, often within a week of starting treatment. BEAM-P will be the first trial to study the effects of BLT on depressive symptoms in cardiovascular patients. Since BLT has not yet been investigated in cardiac patients, the feasibility of conducting a large trial of BLT in this population must be determined in order to avoid potential pitfalls and enhance the chances of success of a full trial.

## 2. BACKGROUND INFORMATION

### 2.1 Summary of Previous Findings

We conducted a non-systematic search of PubMed to identify studies of BLT for non-seasonal depression. We did not identify any studies of BLT for depression in cardiac surgery patients.

However, we found which investigated BLT for depression in other patient populations, such as elderly patients, adolescents, pregnant women, and epilepsy patients. These previous studies generally had a number of serious limitations, including small sample sizes, short treatment and follow-up periods, and inappropriate controls. Blinding was an issue in some studies because differently colored lights (blue, red, green, white) were used. The studies with fewer limitations are described below.

One double-blind RCT investigated the effects of BLT for elderly patients with non-seasonal major depressive disorder. Efficacy was assessed using mean improvement on the Hamilton Rating Scale for Depression scores from baseline to the end of the treatment period (week 3), and to the end of follow-up (week 6). They recruited 89 participants and randomized them to 3 weeks of daily BLT (60 minutes, blue light, 7,500 lux), or placebo (dim red light, 50 lux). Analyses showed significantly greater improvement in the BLT group compared to placebo from baseline to week 3 (43% vs 36%). This improvement was maintained during follow-up (54% vs 33%). BLT also significantly decreased cortisol levels (34% decrease), an indicator of stress, compared to placebo (7% increase). The authors concluded that BLT was effective at reducing depressive symptoms compared to placebo.

A randomized crossover trial took place to investigate the potential of BLT to reduce depressive symptoms in mildly depressed adolescents. After a week of baseline measurements, 28 participants were randomized to receive the therapeutic intervention or the control intervention; half of participants got BLT (2,500 lux) first while half received the dim light (50 lux) first. After 1 week, the participants switched and received the other intervention. The Beck Depression Inventory was used to measure depressive symptoms every week during the trial, and at 1 week post-treatment. The Wilks Lambda test was performed and suggested that there were significant differences between Beck Depression Inventory scores due to the BLT treatment ( $F=3.92$ ,  $p=0.014$ ).

A double-blind RCT for antepartum depression was performed to determine the effects of BLT compared to dim light. For 1 hour per day for 5 weeks, 27 participants used a white light (7,000 lux) or a dim red light (70 lux), depending on group allocation. Depressive symptoms were measured using the Hamilton Depression Rating Scale each week. Analyses showed that BLT treatment was significantly more effective at reducing depressive symptoms compared to the dim light group (effect size 0.78). Significantly more individuals in the BLT group than the control group achieved remission from depression (69% vs 36%).

Finally, a RCT investigated the effect of BLT on symptoms of anxiety and depression. This double-blind study enrolled 101 adults with focal epilepsy. After 12 weeks of being followed, participants received the intervention for 12 weeks: BLT at 10,000 lux for 20-30 minutes per day, or dim light at 2,000 lux for 20-30 minutes per day. Anxiety and depression were measured using the Hospital Anxiety and Depression Scale. No difference in anxiety was found from baseline to end of treatment between the groups. Both groups significantly improved from baseline to end of treatment in depression score. This result may be explained by the fact that 2000 lux (the placebo intervention) has been used as a therapeutic intervention in past studies, and has been shown to be effective. Although 101 participants started this trial, only 58 remained by the end, resulting in a high loss to follow-up rate of 42%. This may be explained in part by the investigators recruiting all patients, regardless of depression status (resulting in less incentive to undergo treatment and remain in the trial). More rigorous, controlled studies are needed to investigate BLT's potential for reducing depressive symptoms in different patient populations. The studies described above had various limitations which the full BEAM Trial will improve upon. We will ensure proper blinding (both lamps will have white light that appears bright), adequate treatment and follow up periods (4, and 52 weeks, respectively), and sufficient sample size. Research investigating BLT for depressive symptoms in cardiac surgery patients is crucial in order to improve patient morbidity and mortality outcomes.

### 3. INVESTIGATIONAL PRODUCTS

|     |                                                |                                                                                                                                                                                                                                                                                                                                                                                                                                                                                                                                                                                                                                                                                                                                                                                                                                                                                                                                                                                                                       |
|-----|------------------------------------------------|-----------------------------------------------------------------------------------------------------------------------------------------------------------------------------------------------------------------------------------------------------------------------------------------------------------------------------------------------------------------------------------------------------------------------------------------------------------------------------------------------------------------------------------------------------------------------------------------------------------------------------------------------------------------------------------------------------------------------------------------------------------------------------------------------------------------------------------------------------------------------------------------------------------------------------------------------------------------------------------------------------------------------|
| 3.1 | Name of Investigational Products        | 
The BEAM-P Trial will use BLT lamps that emit 10,000 lux, and lamps modified to emit 500 lux. These lamps are the TRAVelite lamps manufactured by Northern Light Technologies.
                                                                                                                                                                                                                                                                                                                                                                                                                                                                                                                                                                                                                                                                                                                                                                                                                                 |
| 3.2 | Description of Investigational Products | 
We will be using the TRAVelite Desk Lamp manufactured by Northern Light Technologies, located in Montreal, Quebec. The light is emitted from a lamp. The fluorescent tubes in the box are covered with a diffusing screen to ensure even distribution of light and protection from ultraviolet light. Half of the lamps will emit 10,000 lux, while the rest will be modified to emit 500 lux. Both lamps will look identical and the difference in the light emitted will only be apparent if both lamps are placed next to each other. This will ensure that neither the study personnel nor the participants are aware of the participants' random allocation. These lamps have a diffusing screen covering the bulbs to evenly diffuse the light and protect against ultraviolet rays. These lamps also have a stand which enables users to place the box horizontally or vertically on most surfaces. BLT lamps can be purchased by the public at various stores, including many pharmacies.
 |
| 3.3 | Route of Administration                 | 
Participants will be exposed to the light by sitting 12 inches from the lamp while looking at a surface that the light is reflecting onto. They should not look directly into the light, but may glance at it occasionally. This therapy can be done while reading, eating, or doing other seated activities.
                                                                                                                                                                                                                                                                                                                                                                                                                                                                                                                                                                                                                                                                                                  |
| 3.4 | Dose and Dosage Regimen                 | 
Participants will be instructed to use the light for 30 minutes each morning within an hour of waking, but not past 1:00 pm (to ensure that sleep does not become disturbed). The light must be approximately 12 inches from the participants' faces. Rulers will be used in hospital to ensure participants use the lamp at the proper distance. The length of time, and distance from the lamp both affect the intensity of light being received. Participants' eyes should be open when using the lamp, but they should not look directly into the lamp.
                                                                                                                                                                                                                                                                                                                                                                                                                                                    |
| 3.5 | Product Accountability                  | 
All lamps will be blinded using blind codes. An inventory sheet listing the blind codes will be retained. The lamps will be stored in a locked cabinet inside the investigator's office. An accountability log will be kept to log dispensing of lamps to enrolled participants.
                                                                                                                                                                                                                                                                                                                                                                                                                                                                                                                                                                                                                                                                                                                               |
| 3.6 | Treatment Period                        | 
The treatment period will last 4 weeks and will begin once the participant consents to be in the study, is found to be eligible, and is randomized. The treatment will begin in-hospital and will continue at home after hospital discharge, for the remainder of the 4 weeks.
                                                                                                                                                                                                                                                                                                                                                                                                                                                                                                                                                                                                                                                                                                                                 |

### 3.7 Discontinuation Criteria

Discontinuation of lamp use due to participant preference is permitted. These participants will be requested to continue with study follow-ups as per protocol. No negative consequences are anticipated from abrupt discontinuation of the investigational product. Use of the investigational product should be discontinued if participants experience severe or worsening symptoms: eye pain, photosensitivity, suicidal ideation.

### 3.8 Disallowed Medications

During the 4 week treatment period, participants will be allowed to receive other treatments for depression (standard of care); use of such therapies will be recorded.

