Participants will also be provided with an information sheet containing study procedures and contact information for study personnel. Participants in both groups will begin using the lamps in-hospital and will continue the treatment at home for the remainder of the 4 weeks post-surgery. At baseline, participants will complete the Patient Health Questionnaire 9 (PHQ-9), Depression Anxiety Stress Scale short version (DASS-21), and Short Form (36) Health Survey (SF-36) questionnaire in order to determine index levels of depressive symptomology (PHQ-9, DASS-21) and health-related quality of life (SF-36). A case report form, to collect demographic and clinical information, will be completed at baseline. On day 4 and on the day of discharge, participants will complete questionnaires and a CRF will be completed assessing adherence, tolerability, and side effects. There will be a clinic visit at week 4, when patients will return their lamp and complete questionnaires, and study personnel will complete a case report form to monitor treatment adherence. At week 12, participants will have the option to complete their questionnaires online or by mail. To compensate participants for expenses incurred due to participation (parking, childcare, opportunity costs, etc.), they will receive \$25 at week 4 and a \$20 prepaid VISA card after completing the questionnaires at week 12.

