##### 4.8.2 Exclusion Criteria

- 1) Pregnant or lactating females;
- 2) Medical condition with a prognosis  $< 12$  weeks;
- 3) History of bipolar disorder, SAD, psychosis, or dementia;
- 4) Medical condition contraindicating use of BLT (ocular or retinal pathology: glaucoma, cataracts, retinal detachment, retinopathy, diabetes);
- 5) Medical condition that increases photosensitivity (e.g. systemic lupus erythematosus,

- rosacea, psoriasis, albinism);
- (6) Current use of medication that increases photosensitivity (e.g. St John's Wort, lithium, melatonin, tetracycline, Accutane, Benzoyl peroxide, Retin-A);
- (7) Less than one month following previous BLT;
- (8) Light induced epilepsy or migraines; or
- (9) Suicidal ideation.

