##### 5.4.2 Data Collection

A case report form (CRF) will be completed at baseline, day 4, day of discharge, and week 4. At week 12, participants will complete a survey to provide additional data. At baseline, the CRF will collect demographic and clinical information, including medical history, current medications, surgery details, and depression history. Participants will also complete three questionnaires: SF-36, PHQ-9, and DASS-21. At day 4, day of discharge, and week 4, participants will be asked about protocol adherence, symptoms, and AEs or SAEs. They will also complete the same three questionnaires to assess depressive symptoms and health-related quality of life. At week 12, participants will be asked to complete these same questionnaires as well as a survey assessing symptoms via distance either through mail or an online questionnaire website. During enrollment, participants will be asked about their preference (i.e. mail or online). If they choose the mail option, the questionnaires will be mailed to their address, along with a return envelope and stamp. If they choose the online option, they will be sent an email at week 12. The email will contain a link to the online survey (SurveyMonkey), which they can use to access the survey and complete the questionnaire.

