##### 5.4.3 Source Data

All data collected at baseline and follow-up visits on CRFs and questionnaires will be considered source data. Medical records will also be considered source data.

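### Exclusion 6 bars photosensitising medication at entry, but nothing carries the bar into the 4 weeks of lamp use, and section 3.8, headed Disallowed Medications, disallows nothing

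*Protocol*

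**What the plan says.** Four parts of the protocol bear on this.

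- **Entry (section 4.8.2, criterion 6).** The exclusion reads "Current use of medication that increases photosensitivity (e.g. St John's Wort, lithium, melatonin, tetracycline, Accutane, Benzoyl peroxide, Retin-A". It concerns use at the time of the eligibility check.
- **During treatment (section 3.8, Disallowed Medications).** The only sentence says that in the 4-week treatment period "participants will be allowed to receive other treatments for depression (standard of care); use of such therapies will be recorded".
- **Stopping the lamp (section 3.7).** "Use of the investigational product should be discontinued if participants experience severe or worsening symptoms: eye pain, photosensitivity, suicidal ideation". Participants who stop by preference are asked to stay in follow-up.
- **Recording (sections 5.4.2 and 5.4.3).** "At baseline, the CRF will collect demographic and clinical information, including medical history, current medications, surgery details, and depression history". For the later visits the text is "At day 4, day of discharge, and week 4, participants will be asked about protocol adherence, symptoms, and AEs or SAEs". In addition, "Medical records will also be considered source data".

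Section 5.1 places the first contact before surgery, and section 5.3.1 starts the lamp period after it. Treatment begins in hospital and continues at home (section 3.6).

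**The concern.** The exclusion is about a drug combined with light, and the light exposure comes after entry: 30 minutes each morning, about 12 inches from the face, with eyes open (section 3.4). The entry check removes patients already taking such a drug. It does nothing about a drug started later, and medication can change around cardiac surgery and after discharge.

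The heading of section 3.8 promises the missing rule, but the text beneath it gives only a permission. Staff who follow it as written could let a participant start an agent that the protocol itself treats as unsuitable alongside the lamp, and let lamp use go on. What is at stake is participant safety and clear conduct, in a pilot meant to expose such problems before a full trial. No statistical figure depends on it.

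**Working it through.** The plan states no figure on this point, so the check is a side-by-side reading, followed by one calculation for the cost of the fix.

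1. **Does any section extend exclusion 6 past entry?** The sections that deal with medication, photosensitivity, stopping or follow-up data are 3.7, 3.8, 4.8.2, 5.4.2, 6.1 and 6.2. None does.

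2. **What does section 3.8 disallow?** Nothing. It permits depression treatment and has it recorded. It makes no exception for exclusion-6 agents and is silent on photosensitising drugs given for other reasons.

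3. **Can the permission and the exclusion meet?** Yes, if St John's Wort or lithium is given for depression. That rests on ordinary drug classification; the protocol does not say which treatments count as standard of care. Participants need a PHQ-9 score of at least 8 to enter (section 4.8.1), so depression treatment during the 4 weeks is foreseeable.

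4. **Does the stopping rule fill the gap?** Only in part. Section 3.7 responds to symptoms, not to starting a drug. The protocol does carry another exclusion forward: suicidal ideation is criterion 9 at entry and also a reason to stop the lamp. Criterion 6 has no such counterpart.

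5. **Would a new drug be noticed in time?**
   - A depression therapy would be recorded under section 3.8.
   - An in-hospital order could be traced in the medical records, although no section asks staff to look for it.
   - Section 5.4.2 lists medications at baseline and not at day 4, discharge or week 4. It is a summary, and the CRF is not shown.
   - After discharge, the schedule in section 5.4.4 has no visit until week 4. Section 4.1 says of that visit: "There will be a clinic visit at week 4, when patients will return their lamp and complete questionnaires". A drug started at home might therefore come to light only when lamp use is over, unless symptoms lead to earlier contact.

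6. **What would stopping the lamp cost?** The input is the sample size of 38 (section 4.1). One participant moved from adherent to non-adherent changes the adherence rate by 1/38 = 0.026, or 2.6 percentage points. Two change it by 2/38 = 0.053, or 5.3 points. These are upper limits, because a participant who stops late may still meet the 60% threshold in section 4.4. That section does not say which mornings form the denominator, so no number of tolerable missed mornings is calculated.

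**The case against.** The strongest reply is that the protocol states nothing false. Criterion 6 governs entry and section 3.8 governs depression treatment, so on that view what remains is a loose heading and an unwritten rule. Several safeguards already apply. The lamp's screen protects against ultraviolet light (section 3.2), and no major safety concern is expected (section 3.9). Photosensitivity and eye pain stop the lamp (section 3.7). Adverse events and tolerability are collected at every follow-up (section 6.1), and participants with possibly related adverse events are advised to contact staff about new or worsening symptoms (section 6.2). Section 4.1 adds: "Participants will also be provided with an information sheet containing study procedures and contact information for study personnel". That sheet is not shown and may already give advice on medication.

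Much of this stands, and it keeps the point at low priority. It does not remove it. Of the safeguards in place during lamp use, only the screen acts before symptoms appear. A concomitant-medication rule also belongs in the protocol, under the heading that already exists for it.

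A reader might infer more than the text supports:

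- **That section 3.8 permits photosensitising drugs in general.** It does not. Outside depression treatment it is silent.
- **That the entry bar is useless unless extended.** It already removes everyone taking such drugs at the check. Only new starts during the 4 weeks remain, and no rate is given for them.
- **That a fixed share of the named agents is affected.** The list opens with e.g., so it is not a complete denominator, and the overlap depends on outside classification. The range runs from none of the named agents to three, if melatonin is also counted as a depression treatment.

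**Conclusion.** The point holds as a low-priority safety clarification. Exclusion 6 ends at entry, section 3.8 disallows nothing, and its permission does not except exclusion-6 agents. The text is enough to establish this. That the permission could reach St John's Wort and lithium is an assumption from ordinary drug classification.

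Its size cannot be expressed as a frequency of harm, because the protocol gives neither a rate of new starts nor a rate of harm. A reader might infer that participants are likely to be injured or that the trial's results are at risk. The documents support neither: the safeguards limit the risk, and recruitment rate, the primary endpoint, does not depend on medication taken after randomisation.

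**What to change.** In section 3.8, state three things:

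- Medications meeting exclusion 6 should not be started during the 4 weeks of lamp use.
- Other standard-of-care depression treatment stays allowed and recorded.
- If an exclusion-6 medication is clinically required, it is given and lamp use stops, in either arm, without unblinding and with follow-up continuing as in section 3.7.

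Add one item to the existing day 4, discharge and week 4 CRFs for any newly started exclusion-6 medication.

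The cost is a few lines of text and one item at three visits already scheduled. The downside is an occasional stopped lamp, which may lower the adherence rate by up to 2.6 percentage points per participant affected, assuming all 38 are in the denominator. An instruction to call staff before starting any new medicine at home is not needed; it would go well beyond the problem in patients just discharged after cardiac surgery.
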